### Electroacupuncture interventions

The selection of acupuncture points is semi-structured. Unilateral Shousanli LI10 and Hegu LI4 (on the forearm and hand), and Zusanli ST36 and Fenglong ST40 (on the leg) will be used for EA. Up to eight supplementary acupuncture points will be chosen according to the adverse effects of OM that participants experience during that week. These points are manually needled. In total, up to 12 needles are used for each session. Disposable acupuncture needles of 0.25 mm diameter and 30 or 40 mm length (Hwato, Suzhou Medical Instrument Factory, China) are used.

The real and sham acupuncture procedures follow those described in our previous study [19] and the Standards for Reporting Interventions in Controlled Trials of Acupuncture [24]. Briefly, in the EA group, after needle insertion and de qi sensation is produced, described as a numb, distended and aching sensation, a battery operated electroacupuncture instrument (Model E600 HAN Multi-Purpose Digital Electronic Acupunctoscope, manufactured by Tens Plus Industrial Company, Hong Kong) is connected to the handles of four needles in the main acupuncture points in the extremities to deliver electrical stimulation for 20 minutes. Electrical stimuli will be delivered at an alternating frequency of 2 and 100 Hz every 3 seconds. The intensity of stimulation is strong but comfortable, and adjusted once during the treatment.

For sham EA, a set of sham points are developed to match each real point. Needles are shallowly inserted into the sham points without manipulation. A manufacture modified non-functioning EA stimulator showing a continuously flashing light and emitting a beeping sound is connected to the end of the four needles via wires, and placed on a table within the participant’s sight. De qi sensation is not intended. We have used this procedure previously, and participants could not tell EA from sham EA [19].

The treatment will be given twice a week for four weeks followed by once a week for two weeks then once every two weeks for four weeks. In total, 12 sessions should be delivered within 10 weeks. Participants completing less than 50% of the treatment are considered as non-compliant. Their data will be treated as missing data.

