### Power and sample size calculation

Using sample means from baseline and the end of the treatment phase of the OM consumption data from our pilot study [19], we estimate that a total sample size of 316 will provide 80% power using a 1% level of significance to detect an effect size estimate of 0.48 between the EA and sham EA groups. Because intention-to-treat analysis will be used, no additional participants are required. We plan to recruit 316 participants in total. A dropout rate of 20% is considered to be within the normal range.

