### Randomisation and blinding procedures

After a four-week run-in period, participants who meet all selection criteria are randomly allocated into one of the three groups, namely EA, sham EA or no-EA with a 2:1:1 ratio. An automated telephone randomisation service provided by the National Health and Medical Research Council Clinical Trial Centre at the University of Sydney is used. Before the commencement of the first acupuncture session, the treating acupuncturist dials a toll-free number and enters the identification codes of the trial, the acupuncturist and the site, and the baseline OM weekly dose (morphine equivalent). The participant is then randomly allocated to one of the three groups according to a computer-generated randomisation sequence. The acupuncturist records the allocation in a secure and separate file. The computer-generated randomisation uses stratified permuted blocks to ensure that an equal ratio of participants in EA and sham EA groups in each centre is assigned to each acupuncturist; and to ensure that an equal number of participants consuming high or low dose of OM is assigned to each group. The cut-off OM dose for high or low consumption is 560 mg (morphine equivalents) per week, decided upon by pain specialists on the team based on our pilot study and other published studies reporting average OM consumption by patients with chronic pain [22,23]. Three quarters of the participants are in either the EA or sham EA group and are blinded; one quarter of the participants are in the no-EA group and are be blinded. The success of blinding of the two acupuncture groups is assessed. Details are presented in Assessment of efficacy below.

The acupuncturists and MDs are not involved in outcome assessments. Blinded assessors are required to conduct outcome assessments, collect Medication and Pain Diaries, and check any missing data. The trial data are entered by research assistants and analysed by a statistician. Except for the acupuncturists, all of the above will be are blinded to participant allocation. Professional statistical assistance is also sought to double check the data analysis.

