### Withdrawal

Participants who find their pain significantly worse or cannot tolerate EA may terminate their involvement in the study. They are assessed by one of the MDs with advice on alternative management strategies for their condition. Their data will be treated as missing data.

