### Statistical analysis of the trial outcomes

The Statistical Program for Social Science (SPSS, the latest version) is used for data analyses. Baseline categorical data, demographic characteristics such as gender and age category, and numerical data are analysed with *χ*^2^ tests and one-way analysis of variance, respectively, to determine comparability of the three groups on these variables.

Linear mixed models (for continuous outcome variables) and generalised estimating equations (for categorical outcome variables) are used to examine the changes over time in weekly dosage of OM, numbers and types of OM-related AEs, severity of pain and Beck Depression Inventory. *χ*^2^ tests are also used to detect group differences in the numbers of dropouts and AEs.

Both intention-to-treat and per protocol analyses are used. Data from participants who do not violate the treatment protocols will be included in the per protocol analysis. Missing data are dealt with using the last value carried forward method. Missing Beck Depression Inventory and SF-36 data are dealt with according to the relevant manual.

Apart from the effects of types of intervention, the influence on the outcomes of differences between centres and therapists is also analysed. The relationship between OM reduction and attitude to pain are explored.

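### The rule that treats low attenders' data as missing is not confined to the per-protocol analysis, so the analysis called intention-to-treat could overwrite recorded opioid outcomes according to attendance

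*Protocol article*

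**What the plan says.** Under Electroacupuncture interventions, the protocol article plans 12 sessions over 10 weeks and then states: "Participants completing less than 50% of the treatment are considered as non-compliant. Their data will be treated as missing data". Half of 12 is 6, so the rule covers anyone with fewer than six sessions. It is not tied to any particular analysis set.

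Under Withdrawal, people who leave the study because their pain is significantly worse or because they cannot tolerate EA get the same treatment: "Their data will be treated as missing data".

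Under Statistical analysis of the trial outcomes, the article says: "Both intention-to-treat and per protocol analyses are used". The per-protocol set is made up of participants who kept to the treatment protocol, and missing values are filled by LOCF. Under Power and sample size calculation, the use of ITT is the stated reason for adding no participants to the 316.

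The primary outcome is the change in opioid medication from baseline to the end of treatment, taken from a diary kept daily through weeks 5 to 14 (Primary outcome measure). Blinded assessors collect the diaries (Randomisation and blinding procedures), and a researcher telephones all participants three times during treatment (Pain medication management).

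**The concern.** An ITT analysis compares the groups as randomised, using the outcomes that were observed. Here, attendance after randomisation decides whose recorded outcome is used. Someone with five sessions and a complete week-14 diary would have that diary set aside and an earlier dose carried forward.

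The substitute is not neutral. All arms are asked to taper, with a target of 75% to 100% reduction by week 14, so dose is expected to fall over time in every arm and an earlier value will tend to understate the reduction. If low attendance differs between EA and sham, the replacement can create a difference or hide one.

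The no-EA arm has no sessions during the 10 weeks, so the rule cannot apply there. The third secondary hypothesis (EA plus pain medication management versus pain medication management alone) would be tested with values altered in one arm only.

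**Working it through.** **1. The plan's own figure.** The inputs are "80% power using a 1% level of significance", "to detect an effect size estimate of 0.48 between the EA and sham EA groups" and allocation to "EA, sham EA or no-EA with a 2:1:1 ratio". The article does not state whether the test is two-sided; two-sided is assumed.
- n(sham) = (1 + 1/2) × (2.576 + 0.842)² / 0.48² = 1.5 × 11.68 / 0.2304 ≈ 76.0, and 77 with the small-sample margin used in the check. The total is 4 × 77 = 308, against 316 stated.
- With 316 the arms are 158, 79 and 79, and power is 0.818 (normal) or 0.811 (noncentral t).

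The sample size reproduces. The point is not an arithmetic error in N.

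**2. The passages side by side.**
- Fewer than six sessions: data treated as missing, with no analysis set named.
- Missing data: filled by LOCF.
- ITT: promised, and used to justify no inflation of N.
- Primary outcome: diary-based, so it can be observed whatever the attendance.

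Taken together, a literal reader programming the ITT analysis would replace recorded low-attender values.

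**3. Illustration of size.** The documents give no rate of low attendance, so everything here is assumed:
- no true effect;
- a 32% mean reduction in all participants, low attenders included (midpoint of the pilot's 39% and 25%);
- SD = 14 / 0.48 ≈ 29.2 points, which supposes that 0.48 corresponds to the pilot's 14-point contrast (39 − 25);
- affected values reset fully to baseline, the extreme case;
- EA 158, sham 79.

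Standard error in SD units: √(1/158 + 1/79) = 0.1378.
Spurious difference = (sham rate − EA rate) × 32.
Shift in SE units = difference / 29.2 / 0.1378.
Type I error = P(|Z + shift| > 2.576).

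| EA vs sham affected | Spurious difference (points) | Shift (SE) | Type I error |
|---|---|---|---|
| equal rates | 0 | 0 | 1.0% |
| 15% vs 20% | 1.6 | 0.40 | about 1.6% |
| 15% vs 25% | 3.2 | 0.80 | about 3.8% |
| 10% vs 25% | 4.8 | 1.19 | about 8.4% |

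With more low attenders in sham, the spurious difference favours EA. With more in EA, it goes the other way.

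**4. Sensitivity.** If low attenders achieve half the reduction (16%), 15% versus 25% gives 0.10 × 16 = 1.6 points and about 1.6%. If LOCF carries a partly reduced dose rather than baseline, the shift is again smaller.

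**5. EA versus no-EA.** On the same assumptions, resetting 15% of EA alone moves the contrast by 0.15 × 32 = 4.8 points, against EA.

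**The case against.** The strongest reply is that the 50% rule was meant to define the per-protocol set. It is the only compliance threshold in the article, the per-protocol definition gives none of its own, and the article commits to ITT twice. That reading is possible, but it is not written. The per-protocol set is already formed by leaving out protocol violators, so there would be no need to declare anyone's data missing. If that was the intention, one sentence settles it.

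A second reply is that LOCF keeps everyone in the analysis. It keeps the headcount, but attendance still decides whose real outcome counts.

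Third, attendance may be nearly equal in EA and sham. Both groups are blinded, and the authors report that participants could not tell the procedures apart. This stands: with equal rates and equal outcomes, the illustration gives no EA-sham bias.

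Four stronger readings that a reader might infer are not supported:
- **That type I error is roughly quadrupled.** The 3.8% comes from one unsourced pair of rates with a full reset to baseline.
- **That many low attenders will have a recorded week-14 dose.** The diary makes this possible, but no document says how many there are or whether they keep the diary.
- **That the Withdrawal section makes the same error.** It concerns people who end their involvement in the study, whose later values are probably never collected. Only values recorded before they left are in doubt.
- **That the comparison with no-EA is tilted towards EA.** It is a secondary comparison, and on these assumptions the shift goes against EA.

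**Conclusion.** The point holds as a matter of what the text permits. Read as written, the article allows recorded outcomes of low attenders to be replaced in the ITT analysis, which conflicts with its own ITT commitment and with the reason given for not inflating N. It also treats the no-EA arm differently from the other two.

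The size and direction of any bias cannot be derived from the documents. On the stated assumptions, the EA-sham effect runs from none (equal rates) to 4.8 points and about 8.4% type I error (10% versus 25%). It is smaller if low attenders reduce less or if the carried value is already partly reduced. The case for change rests on the conflict between the sections, not on any one of these scenarios.

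**What to change.** - Under Electroacupuncture interventions, delete the sentence that treats non-compliant participants' data as missing, and use the 50% rule only to define the per-protocol set.
- Under Statistical analysis of the trial outcomes, name ITT as primary. State that it uses every recorded value of every randomised participant, whatever the number of sessions attended.
- State that diary collection continues after treatment is stopped, unless consent to data collection is withdrawn.
- Under Withdrawal, state separately that values recorded before a participant leaves the study are kept, and that only values not collected afterwards are missing.

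The cost is mainly wording, since the diaries and telephone contacts already exist. The small downside is continued diary collection from people who have stopped treatment.

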### Pain medication management

PMM is an integral part of pain management in multidisciplinary clinics. In this trial, PMM consists of patient education about pain and pain medications, and advice on OM reduction. A *Pain and Medication Management Information Brochure* has been developed to standardise PMM across all centres. In the fifth week, MDs explains to participants the impact of chronic pain, and the potential problems associated with OMs. OM reduction schedules are developed and explained to each participant at the interview. The schedule is flexible and individually tailored. It includes instructions for which type of OM to reduce first, how much and when, the alternative medications and what to do if pain increases. In general, short-acting OMs are reduced first, then the long-acting (slow-release) OMs. Participants are asked to reduce their OM dosage by 30% in week 8, 50% by week 11 and 75% to 100% by Week 14. Participants are asked to reduce OM as long as their pain is not worse. If increased pain causes distress or dysfunction, participants can increase their OM dose to the previous level or take alternative non-opioid medications prescribed by MDs. Clonidine may be prescribed for participants experiencing opioid withdrawal symptoms as judged by the MDs. The dosages of all pain relief medications are recorded.

As part of PMM, during the 10-week treatment and the three-month follow-up periods, a trained researcher will make a phone call to all participants three times during the treatment and once a month during the follow-up period to remind participants of the OM reduction schedule. During the trial period, participants are instructed to continue their routine therapies.

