#### *Primary outcome measure*

The primary outcome measure is the change in OM between baseline and the end of the treatment period. OM usage is recorded daily in the Medication and Pain Diaries during the run-in period (between the first and fourth weeks), treatment period (between the 5^th^ and 14^th^ weeks) and follow-up period in the 18^th^, 22^nd^ and 26^th^ weeks. To make meaningful comparisons on medication use, the dosage of OM will be converted into morphine equivalent dose for data analysis [25].

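### The 50% attendance rule can be failed only in the EA and sham EA arms, so a per-protocol test of EA against pain medication management alone (hypothesis 3) compares selected with unselected participants, and the rule's missing-data clause carries the same imbalance into intention-to-treat

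*Protocol article*

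**What the plan says.** The section on electroacupuncture interventions sets the session plan: "twice a week for four weeks followed by once a week for two weeks then once every two weeks for four weeks". It gives the total as "In total, 12 sessions should be delivered within 10 weeks". It then states the attendance rule, "Participants completing less than 50% of the treatment are considered as non-compliant", and its consequence, "Their data will be treated as missing data". No matching rule is given for the no-EA arm or for attendance at pain medication management.

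The statistical analysis section uses both intention-to-treat and per-protocol analyses and does not rank them. It describes the second set in one sentence: "Data from participants who do not violate the treatment protocols will be included in the per protocol analysis". It does not say which pairs of arms the per-protocol analysis covers. It fills missing data by last value carried forward.

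The Aims section lists, as secondary hypothesis 3, that EA combined with pain medication management is better than pain medication management alone for opioid use and adverse events. The Withdrawal section allows participants whose pain becomes significantly worse, or who cannot tolerate EA, to leave the study.

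**The concern.** A per-protocol comparison is interpretable only if the filter acts in much the same way on both sides. For EA versus sham EA it does: both arms have 12 planned sessions and the same threshold. For EA versus no-EA it does not, because a session count can exclude people from one side only.

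Attendance is unlikely to be unrelated to outcome. The protocol itself names worse pain as a reason for stopping, and a person in worse pain is also less likely to have cut opioids. Removing such people from EA while keeping their counterparts in no-EA would make EA look better even if it did nothing.

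The sentence that turns non-compliers' data into missing data adds a second problem. It is not tied to the per-protocol set. Taken at face value, diary records that were actually collected would be discarded and replaced by a carried-forward value, again only in the two acupuncture arms. Intention-to-treat as written would therefore not be a clean fallback for hypothesis 3.

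**Working it through.** **1. The plan's own figure.** Sessions: 2 × 4 + 1 × 2 + 4/2 = 8 + 2 + 2 = 12, over 4 + 2 + 4 = 10 weeks. This matches the stated 12 sessions in 10 weeks. Half of 12 is 6, so a participant with 5 or fewer sessions is non-compliant.

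**2. Who can fail the rule.** Arm sizes follow from 316 participants at 2:1:1.

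| Arm | Participants | Planned sessions | Can fail the rule? |
|---|---|---|---|
| EA | 158 | 12 | yes |
| Sham EA | 79 | 12 | yes |
| No-EA | 79 | 0 | no |

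**3. Size of the selection effect, EA versus no-EA.** The article gives no figure for poor attendance or for how poor attenders fare, so these are assumptions:
- no true difference between EA and no-EA;
- a share p = 0.20 of EA excluded for attendance;
- those excluded would have done δ = 0.3 to 0.8 SD worse than those kept;
- nobody excluded from no-EA on this criterion.

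The full EA mean is (1 − p) × kept + p × excluded, so the kept mean exceeds the full mean by p × δ:
- δ = 0.3: 0.20 × 0.3 = 0.06 SD
- δ = 0.8: 0.20 × 0.8 = 0.16 SD

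**4. Effect on the test.** After exclusion EA has 0.80 × 158 ≈ 126 and no-EA has 79. The standard error in SD units is √(1/126 + 1/79) = 0.1435, with 203 degrees of freedom. The non-centrality is shift/0.1435. The sample-size section uses a 1% level for EA versus sham EA without stating sidedness. I assume two-sided, apply it to hypothesis 3, and show 5% as well.

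| Spurious shift | Non-centrality | Rejects at nominal 1% | Rejects at nominal 5% |
|---|---|---|---|
| 0.06 SD | 0.42 | 1.7% | 7.0% |
| 0.16 SD | 1.11 | 7.1% | 19.9% |

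**5. The route into intention-to-treat.** Three statements meet: fewer than half the sessions makes a participant non-compliant; a non-complier's data are treated as missing; missing data are carried forward from the last value. Together they replace observed opioid doses in EA and sham EA and cannot do so in no-EA. The direction of this second distortion is not fixed by the text. Carrying forward an early, higher dose would understate reduction in EA; carrying forward a low dose from before a relapse would overstate it. I have therefore put no figure on it.

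**The case against.** The strongest reply is that the per-protocol set is defined by not violating the treatment protocols, and the 50% rule is not named there. No-EA participants could violate the protocol in other ways, for instance by missing the week 5 pain medication management interview or by changing co-interventions. The detailed set definition may also stand in an analysis plan that is not shown. Further, hypothesis 3 is secondary, some asymmetry is common whenever a treated arm is compared with an untreated one, and intention-to-treat is reported too.

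Part of this stands. The text does not prove that attendance defines the per-protocol set, and other criteria could exclude no-EA participants. But a shared criterion does not cancel a one-sided one: if attendance counts at all, it still filters only the acupuncture arms. The protocol itself, not an unseen plan, fixes the threshold and its missing-data consequence. Intention-to-treat answers the objection only once that consequence is removed. It is also fair that 20% and 0.3 to 0.8 SD have no source in the article; they illustrate scale and predict nothing.

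A reader might go further. With treatment in weeks 5 to 14 and full attendance, the sixth session falls at the end of week 7, while the reduction targets read "Participants are asked to reduce their OM dosage by 30% in week 8, 50% by week 11 and 75% to 100% by Week 14". One could infer that the per-protocol set is faulty because it keeps people who had no EA during the opioid reduction. The documents do not support that. Nothing says the per-protocol analysis should isolate EA given during the reduction. Week 8 is only the first dated target, on a schedule set individually in week 5. End of week 7 is the earliest date, needing every session attended from a week 5 start. Requiring attendance from week 8 on would itself select on behaviour while pain may be worsening, and so could add bias to EA versus sham EA.

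**Conclusion.** The point holds for hypothesis 3. A per-protocol comparison of EA with pain medication management alone that uses the attendance rule is not like with like, and the likely direction favours EA. The direction is a reasoned expectation from the Withdrawal section rather than a certainty, since some people may stop because they feel better.

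Under the assumptions shown, the spurious difference is modest (0.06 to 0.16 SD), but it raises false-positive rates from 1% to between 1.7% and 7.1%, or from 5% to between 7.0% and 19.9%. Smaller exclusion rates, or poor attenders who do no worse than others, would shrink it towards nothing.

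The missing-data clause is a separate defect of wording. Read literally, it brings the one-sided rule into intention-to-treat. It does not create this between-arm imbalance for the primary comparison, because EA and sham EA share the rule.

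**What to change.** Three changes of wording, none touching the session plan or the opioid schedule:

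1. Base hypothesis 3 on intention-to-treat, using all diary data actually collected regardless of the number of sessions attended.
2. In the section on electroacupuncture interventions, stop treating non-compliers' data as missing. State instead that low attendance affects membership of the per-protocol set only.
3. In the statistical section, confine the attendance-based per-protocol analysis to EA versus sham EA. If a three-arm per-protocol set is wanted, define it only by criteria that every arm can fail, for example week 5 pain medication management interview attended and diary kept.

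The cost is that hypothesis 3 will have no attendance-based per-protocol result. No new data are needed: the diaries already record opioid use in all arms.
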